## Statistical analysis plan

All outcomes will primarily be analysed using an intention-to-treat approach, i.e. all study subjects will belong to the treatment group (exercise intervention or control) they were assigned to, disregarding compliance. As sensitivity analysis, all outcomes will also be analysed using a per-protocol approach, meaning that participants in the intervention group who comply with less than 65% of the prescribed physical exercise program or complete less than 40% of the planned neo-adjuvant systemic therapy (around two 3-weekly courses) will be excluded from analysis.

*Covariate adjustment in statistical models*

Guidelines from the European Medicines Agency (EMA) regarding statistics and covariate adjustments recommend that factors that are used to stratify the randomization, i.e. site of treatment and biological tumour type in this trial, should be accounted for in the statistical analysis^35,36^. However, it is also recognized that “limited numbers of subjects per centre will make it impracticable to include the centre effects in the statistical model”. In this trial it is very likely that some of the centres will contribute few patients, which may cause problems in some of the statistical models, in particular for the categorical outcomes (such as the primary endpoint, pCR) where the variability in the outcome may be too small within each site. Hence, the statistical models, described below, will primarily be adjusted for biological tumour type and not for study site. If appropriate and if the data allows (i.e. no convergence problems and not too small subgroups), the site effect will also be incorporated in the models as a random effect in the mixed models and as a fixed factor in the remaining logistic regression models.

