#### Secondary endpoints

1. *Residual Cancer Burden (RCB)*

Residual Cancer Burden (RCB) is measured as four ordered categories (RCB-0 which corresponds to pCR, RCB-I, RCB-II, and RC-III) at histopathological assessment of the surgical specimen. An ordinal regression model, adjusting for biological tumour type (stratification factor in the randomization), will be used to analyse differences between the treatment arms. If the proportional odds assumption of the model is violated, a nominal regression model or a generalized logistic model will be used instead if appropriate.

1. *Objective tumour response*

Response Evaluation Criteria in Solid Tumours (RECIST) will be applied in order to assess change in radiological tumour size (%) from baseline to pre-surgery imaging. RECIST criteria classify response into four ordinal outcome categories: complete response, partial response, stable disease and progressive disease (see page 18)^31^. An ordinal regression model, adjusting for biological tumour type (stratification factor in the randomization), will be used to analyse differences between the treatment arms. If the proportional odds assumption of the model is violated, a nominal regression model or a generalized logistic model will be used instead if appropriate. Tumour size at histopathological assessment of the surgical specimen may be included in comparative analyses. Mean difference in reduction of tumour size between treatment arms will be analysed with an ANOVA, including biological subtype as a factor in the model.

1. *Survival outcomes*

All-cause, breast cancer-specific and recurrence-free survival will be analysed at 2, 5 and 10 years. Contralateral breast cancer is not regarded an event. Difference in time-to-event outcomes between treatment arms will be compared. The mortality outcomes are defined as time from date of randomisation to death (from any cause or breast cancer as underlying cause, respectively) or censoring at end of follow-up. For recurrence-free survival, the outcome is measured as time from date of randomisation to breast cancer relapse or censoring at end of follow-up. Survival estimates after 2, 5 and 10 years of follow-up will be compared using Kaplan-Meier estimates. Furthermore, a Cox regression model, adjusting for biological subtype will also be used.

1. *Health-related quality of life*

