5. Sick leave is a patient-reported singular measurement at pre-surgery and at 1- and 2-year follow-up (% sick leave). Mean sick leave proportions will be compared between the treatment arms at each time point using a mixed model for repeated measures (MMRM). Treatment, visit, treatment visit interaction and the stratification factor biological tumour type will be included in the model as fixed effects, and patient as a random effect. An unstructured covariance matrix will be used to model the within-subject error. If the fit of the chosen structure fails to converge, the following covariance structures will be evaluated, in order, until convergence is reached: toeplitz with heterogeneity, autoregressive with heterogeneity, toeplitz, autoregressive and compound symmetry. Additionally, since the outcome is most likely not normally distributed, a non-parametric Kruskal-Walllis test will be performed at each time as a sensitivity analysis.
6. *Device-measured physical activity level*

Several continuous outcome measures from the Fitbit activity tracker will be assessed: 1) METs (metabolic equivalents) in low, medium and high intensity activities, respectively, 2) step counts per day and 3) daily active minutes. The main interest is to see if there is a difference between the treatment arms regarding change of physical activity from baseline to pre-surgery (i.e. after intervention and chemotherapy), but also at 1-year follow-up. A mixed model for repeated measures (MMRM) with treatment, visit and the stratification factor biological subtype as fixed effects, and patient as a random effect. An unstructured covariance matrix will be used to model the within-subject error. If the fit of the chosen structure fails to converge, the following covariance structures will be tried, in order, until convergence is reached: toeplitz with heterogeneity, autoregressive with heterogeneity, toeplitz, autoregressive and compound symmetry. Additionally, heart rates at equivalent exertion levels (assessed on the Borg scale) during physical activity will be explored.

1. *Muscle strength*

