#### Reporting

For the secondary outcomes, the differences between the treatment arms will be reported as an effect measure (e.g. odds ratio or mean difference) together with a complementary confidence interval and a two-sided statistical test of the effect parameter. A Bonferroni corrected significance level will be used.

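### The rank test that backs up the sick-leave model drops tumour type, the stratification factor the model adjusts for; stratifying it is a free improvement

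*Protocol*

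**What the plan says.** Sick leave is the fifth toxicity-related outcome in the protocol (Secondary endpoints). Patients report it as a percentage before surgery and at 1 and 2 years. The main analysis is a mixed model for repeated measures that compares arm means at each of these three visits. On its covariates the protocol says: "Treatment, visit, treatment visit interaction and the stratification factor biological tumour type will be included in the model as fixed effects".

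The same item then adds a check: "since the outcome is most likely not normally distributed, a non-parametric Kruskal-Walllis test will be performed at each time as a sensitivity analysis". It names no stratum, covariate or effect estimate for that check.

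Three other places bear on this choice:

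- **Statistical analysis plan, covariate adjustment.** The protocol cites regulatory guidance on this: "factors that are used to stratify the randomization, i.e. site of treatment and biological tumour type in this trial, should be accounted for". It then sets its own course: models are adjusted primarily for tumour type, and site enters only if the data allow.
- **Reporting.** Arm differences in secondary outcomes "will be reported as an effect measure (e.g. odds ratio or mean difference) together with a complementary confidence interval"; each also gets a two-sided test.
- **Secondary endpoints, RCB and objective tumour response.** For these ordered outcomes the plan is: "An ordinal regression model, adjusting for biological tumour type (stratification factor in the randomization), will be used to analyse differences between the treatment arms".

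**The concern.** A sensitivity analysis is easiest to read when it relaxes one assumption and keeps the rest. This one is there to relax normality, but it also removes the tumour-type adjustment. If the mixed model shows an arm difference and the rank test does not, the reader cannot say which of the two changes is responsible.

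The direction of the possible error is known. Randomisation is stratified by tumour type, so the arms are balanced on it and any difference between tumour types cancels out of the arm comparison. An unstratified rank test still counts that difference as noise. If tumour type predicts sick leave, the test therefore rejects too rarely, and a real effect could be called not robust because of the check.

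**Working it through.** **The plan's own figure.** The protocol states no sample size or power for sick leave. Its only sizing figure is for pCR: 30% v 40%, 80% power, two-sided 5%. With pooled variance,

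n per arm = [1.960·√(2·0.35·0.65) + 0.8416·√(0.30·0.70 + 0.40·0.60)]² / 0.10² = (1.3221 + 0.5646)² / 0.01 = 355.9, so 356 per arm and 712 in total.

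This matches the protocol. The figure of 712 is used below only as the number of patients analysed.

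**What the test is.** With two groups, Kruskal-Wallis is the Wilcoxon rank-sum test. On one simulated two-arm data set both gave p = 0.8694. It tests for a shift in ranks and has no place for tumour type.

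**What dropping tumour type does, by formula.** Let R² be the share of sick-leave variance explained by tumour type. With allocation balanced within tumour type, the true variance of the arm contrast is about (1 − R²) times the variance that the unstratified test assumes. Its true type I error at a nominal 5% is then about 2Φ(−1.96/√(1 − R²)):

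- R² = 0.023: 1.96/0.988 = 1.983, giving 4.7%
- R² = 0.086: 1.96/0.956 = 2.050, giving 4.0%
- R² = 0.231: 1.96/0.877 = 2.235, giving 2.5%
- R² = 0.395: 1.96/0.778 = 2.520, giving 1.2%

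This is approximate, because R² is on the percentage scale and the test works on ranks.

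**The same by simulation.** From the protocol: 712 patients, 1:1 allocation, four tumour types as strata. Assumed, because the documents give nothing:

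- sick leave at 0/25/50/75/100% with shares 30/10/15/10/35%;
- a tumour-type mix of 40/20/10/30%;
- an arm effect of 0.22 SD on the latent scale;
- R² varied from 0 to 0.40.

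One visit, nominal two-sided 5%, 4000 runs per setting; hospital was not simulated. The comparator is the van Elteren test, a rank-sum test stratified by tumour type.

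| R² | Type I error, unstratified | Type I error, stratified | Power, unstratified | Power, stratified | Power lost (points) |
|---|---|---|---|---|---|
| 0 | 5.5% | 5.5% | 75.0% | 74.8% | −0.2 |
| 0.02 | 5.0% | 5.1% | 74.7% | 75.6% | 0.9 |
| 0.09 | 4.4% | 5.3% | 70.7% | 73.8% | 3.1 |
| 0.23 | 2.5% | 4.8% | 61.9% | 71.3% | 9.4 |
| 0.40 | 1.0% | 4.6% | 45.4% | 67.3% | 21.9 |

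Monte Carlo 95% error is about 0.7 points for type I error and 1.5 points for power. Simulation and formula agree within that error. A linear model adjusted for tumour type, run on the same clearly non-normal data, kept type I error between 4.9% and 5.6%.

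**The case against.** The strongest reply is that nothing here contradicts the protocol, and most of it stands.

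- **Reporting.** A reader might infer that a test giving only a p-value breaches the reporting rule. It does not. The mixed model supplies the effect measure and confidence interval, and the rule does not ask each supporting test to supply its own.
- **Usefulness.** A reader might infer that the rank test cannot check the mixed model at all. It can: it shows whether evidence of an arm difference survives without normality, and its conservatism cannot create a false positive. What it cannot do is confirm the size of the adjusted mean difference.
- **Loss of power.** A reader might take the loss as established. It is conditional on a link between tumour type and sick leave that the documents do not quantify. If the link is weak, the loss is negligible.
- **Hospital.** A reader might fault the test for ignoring hospital as well. The protocol leaves site out of its models by default and gives its reason, small centres. The 11 to 17 sites in the Time plan, times four tumour types, would make 44 to 68 cells, or about 10 to 16 of 712 patients per cell. The inconsistency concerns tumour type only.
- **Unseen SAP.** A separate SAP may already stratify the test, and then nothing needs changing. But the protocol itself names the method, and Kruskal-Wallis in its ordinary form is unstratified.

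What the reply does not remove is that the check drops the one factor which the main sick-leave model includes, when a version that keeps it is just as easy to run.

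**Conclusion.** The point holds as a small, free improvement. The prescribed check is unstratified, while the main model and the protocol's general approach adjust for tumour type. The cost is about 0 to 1 point of power if tumour type explains up to 2% of sick-leave variance, about 3 points at 9% and about 9 points at 23%. The 40% row in the table only shows the trend; nothing in the documents makes it likely.

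These figures rest on the assumed outcome distribution, tumour-type mix and arm effect, on 712 patients at a single visit, and on a nominal 5% level. The protocol applies a Bonferroni correction to secondary outcomes without stating the divisor, so absolute power would differ. The type I error figures rest mainly on R².

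The documents do not support a claim that the test is in fact underpowered or that a reporting rule is broken. One sensitivity analysis of one secondary toxicity item is affected. The primary endpoint, the sample size and the main sick-leave estimate are not.

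**What to change.** Replace the Kruskal-Wallis sentence with: *As a sensitivity analysis, sick leave at each visit will be compared between arms by a van Elteren test (Wilcoxon rank-sum test stratified by biological tumour type).* Hospital should not be a stratum by default, in line with the protocol's own choice.

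Optionally, add the ordinal regression adjusted for tumour type that is already planned for RCB and objective tumour response, reported as an odds ratio with a confidence interval. This gives the check an estimate, which van Elteren alone does not. It rests on proportional odds, however, and does not estimate the mean difference.

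After the change a disagreement with the mixed model can no longer come from the dropped adjustment. It could still come from comparing ranks rather than means, or from testing visits one at a time instead of jointly, which loses the mixed model's handling of missing values.

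The cost is one sentence. Tumour type is already recorded for randomisation, and where it does not predict sick leave the stratified test gives up essentially nothing (74.8% v 75.0% power).

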All health-related quality of life outcomes are measured as scores that range from 0 to 100, hence the outcomes are continuous. Both the global QoL score as well as the 17 subscales (8 scales reflecting symptoms and 9 reflecting function) will be assessed at four time points: baseline, pre-surgery, 1 and 2 years after surgery. To evaluate QoL scores at each time point both within and between the treatment groups, a mixed model for repeated measures (MMRM) will be used. Treatment, visit, treatment visit interaction and stratification factor biological tumour type will be included in the model as fixed effects, and patient as a random effect. An unstructured covariance matrix will be used to model the within-subject error. If the fit of the chosen structure fails to converge, the following covariance structures will be evaluated, in order, until convergence is reached: toeplitz with heterogeneity, autoregressive with heterogeneity, toeplitz, autoregressive and compound symmetry. Furthermore, differences in change from baseline between the treatment arms will be assessed at each time point by constructing relevant contrasts of the estimated regression coefficients.

1. *Self-reported physical activity*

Physical activity is reported using the Godin-Shephard Leisure-Time Physical Activity Questionnaire (GSLTPAQ) as total minutes per week of training in three intensity levels (light, moderate and intensive) and for weight training. Hence, the outcome is continuous. A mixed model for repeated measures (MMRM) will be used to assess physical activity at four different time points: baseline, pre-surgery, 1 and 2 years after surgery). The model will include treatment, visit, treatment-visit interaction and the stratification factor biological tumour type as fixed effects, and patient as a random effect. An unstructured covariance matrix will be used to model the within-subject error. If the fit of the chosen structure fails to converge, the following covariance structures will be evaluated, in order, until convergence is reached: toeplitz with heterogeneity, autoregressive with heterogeneity, toeplitz, autoregressive and compound symmetry. Physical exercise will be assessed both within and between the treatment groups. Furthermore, differences in change from baseline between the treatment arms will be evaluated at each time point by constructing relevant contrasts of the estimated regression coefficients.

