3. Objective cognitive dysfunction is measured by an online neuropsychological test (Amsterdam Cognition Scan) at baseline and 1-year follow-up. The total Amsterdam Cognition Scan (ACS) score, calculated as the mean of the (reversed) z-scores of all main online neuropsychological outcome measures, will be of primary interest. Furthermore, separate z-scores of the cognitive tests will also be assessed. Hence, the measured cognitive dysfunction outcomes, measured at baseline and at 1-year follow-up, are continuous variables. A mixed model for repeated measures (MMRM) will be used to assess change from baseline of ACS scores, which is the primary interest. The model will include treatment, visit and the stratification factor biological tumour type as fixed effects, and patient as a random effect. An unstructured covariance matrix will be used to model the within-subject error. If the fit of the chosen structure fails to converge, the following covariance structures will be evaluated, in order, until convergence is reached: toeplitz with heterogeneity, autoregressive with heterogeneity, toeplitz, autoregressive and compound symmetry. ACS scores will be assessed both within and between the treatment groups.
4. Cardiovascular toxicity is a dichotomous outcome (yes/no) that will be evaluated only in the subgroup of patients with HER2-positive tumours who are treated with anti-HER2 therapies (approximately 30% of the study population). A multivariable logistic regression model, adjusting for biological tumour type will be used to assess differences between the treatment arms.

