The muscle strength is measured on a continuous score on each arm and leg. The main interest is to see if there is a change in strength after intervention, i.e. change from baseline to pre-surgery. A mixed model for repeated measures (MMRM) with treatment, visit and the stratification factor biological tumour type as fixed effects, and patient as a random effect. An unstructured covariance matrix will be used to model the within-subject error. If the fit of the chosen structure fails to converge, the following covariance structures will be tried, in order, until convergence is reached: toeplitz with heterogeneity, autoregressive with heterogeneity, toeplitz, autoregressive and compound symmetry.

1. *Cardiorespiratory fitness*

The Åstrand submaximal cycle test renders a continuous outcome. The main interest is to see if there is a change in cardiorespiratory fitness after intervention, i.e. change from baseline to pre-surgery. A mixed model for repeated measures (MMRM) with treatment, visit and the stratification factor biological tumour type as fixed effects, and patient as a random effect. An unstructured covariance matrix will be used to model the within-subject error. If the fit of the chosen structure fails to converge, the following covariance structures will be tried, in order, until convergence is reached: toeplitz with heterogeneity, autoregressive with heterogeneity, toeplitz, autoregressive and compound symmetry.

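### Four secondary-endpoint models (cognition, Fitbit activity, muscle strength, fitness) omit the treatment-by-visit interaction, so as written they cannot estimate the between-arm difference in change from baseline

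*Protocol*

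**What the plan says.** All references are to the protocol's Statistical analysis plan section, under Secondary endpoints, unless stated.

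**Models without the interaction**
- Cognition (Toxicity-related outcomes, item 3): "The model will include treatment, visit and the stratification factor biological tumour type as fixed effects, and patient as a random effect". The aim is that the model "will be used to assess change from baseline of ACS scores, which is the primary interest". The item adds that scores are assessed within and between the groups. There are two visits: the outcomes, "measured at baseline and at 1-year follow-up, are continuous variables".
- Device-measured physical activity (Fitbit): "with treatment, visit and the stratification factor biological subtype as fixed effects, and patient as a random effect". The main interest is a "difference between the treatment arms regarding change of physical activity from baseline to pre-surgery", and also the position at 1 year.
- Muscle strength and cardiorespiratory fitness: both "with treatment, visit and the stratification factor biological tumour type as fixed effects, and patient as a random effect". Each names change from baseline to pre-surgery as the main interest. Neither says there that the change is to be compared between arms.

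**Models with the interaction**
- Health-related quality of life: "Treatment, visit, treatment visit interaction and stratification factor biological tumour type will be included in the model as fixed effects".
- Self-reported activity and sick leave list the same terms.
- The quality-of-life and self-reported activity texts also call for contrasts giving the between-arm difference in change from baseline at each time point.

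**What is to be reported**
- The Reporting section says that differences between the arms will be given and tested for the secondary outcomes, at a Bonferroni-corrected level.
- Hypothesis 2 is that exercise improves these outcomes relative to control.

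**The concern.** A visit effect, a patient effect and an unstructured within-patient covariance make sense only if each patient contributes several scores, baseline among them. In such a model, treatment plus visit without their product says that the arms differ by the same amount before the intervention as after it, and that both arms change equally over time. Randomisation makes the baseline difference zero in expectation, so the model pulls the post-intervention difference towards zero. It also contradicts the stated wish to look at cognition within each group, because it allows only one common change.

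At stake is the reading of four named secondary endpoints. Measured activity, strength and fitness are also the evidence on whether the exercise programme changed anything physiologically. A real effect on them could be reported as small or null, which would in turn colour the interpretation of the pCR result.

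**Working it through.** **1. The plan's own figure.** The protocol gives no effect size, SD, correlation or power for these four outcomes. Its only design figure is for pCR, 30% against 40%, two-sided 5%, 80% power: n per arm = (1.96·√(2·0.35·0.65) + 0.8416·√(0.3·0.7 + 0.4·0.6))² / 0.10² = (1.3221 + 0.5646)² / 0.01 ≈ 356, or 712 in total, as stated. I use 356 per arm below for illustration only.

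**2. What the written model allows.** Write the mean as μ + β·arm + γ(visit) + tumour-type effect. The change in the exercise arm is (γ1 + β) − (γ0 + β) = γ1 − γ0. The change in the control arm is also γ1 − γ0. The between-arm difference in change is therefore 0 whatever the data show.

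**3. What β estimates with two visits (cognition, strength, fitness).** Under generalised least squares, β is a weighted mean of the arm differences at each visit, with weights S⁻¹1 / (1′S⁻¹1), where S is the within-patient covariance. Let the baseline difference be 0, the later difference d, the SDs s0 and s1, and the correlation ρ. The expected share of d recovered is

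(s0² − ρ·s0·s1) / (s0² + s1² − 2ρ·s0·s1).

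With s0 = s1 this is (1 − ρ) / (2 − 2ρ) = 0.50 at any ρ. For unequal SDs (assumed values, s0 = 1):

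| s1/s0 | ρ = 0.5 | ρ = 0.7 |
|---|---|---|
| 0.9 | 0.55/0.91 = 0.60 | 0.37/0.55 = 0.67 |
| 1.0 | 0.50 | 0.50 |
| 1.1 | 0.45/1.11 = 0.41 | 0.23/0.67 = 0.34 |

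Over a wider assumed range (ratio 0.8 to 1.25, ρ 0.3 to 0.8) the share runs from 1.0 down to 0.0.

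**4. Fitbit, three visits (baseline, pre-surgery, 1 year), equal SDs.** Let f be the 1-year effect as a fraction of the pre-surgery effect. Under compound symmetry the weights are 1/3 each, so the share of the pre-surgery effect is (1 + f)/3. Under first-order autoregression with ρ = 0.6 the weights are 0.417, 0.167 and 0.417, so the share is 0.167 + 0.417f.

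| Effect at 1 year | Compound symmetry | Autoregressive 0.6 |
|---|---|---|
| persists (f = 1) | 0.67 | 0.58 |
| halves (f = 0.5) | 0.50 | 0.38 |
| vanishes (f = 0) | 0.33 | 0.17 |

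**5. Power, two visits, equal SDs.** Assume a true effect of 0.2 SD, 356 per arm with complete data, and an unadjusted two-sided 5% test. In SD units, Var(β) = ((1 + ρ)/2)·(2/356) and Var(change contrast) = 2(1 − ρ)·(2/356).
- ρ = 0.5: written model z = 0.10/√(0.75·2/356) = 1.54, power 34%. Change contrast z = 0.20/√(1.0·2/356) = 2.67, power 76%.
- ρ = 0.7: written model z = 0.10/√(0.85·2/356) = 1.45, power 30%. Change contrast z = 0.20/√(0.6·2/356) = 3.44, power 93%.

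Whatever the effect size, the ratio of the two z-values is √((1 − ρ)/(1 + ρ)): 0.58 at ρ = 0.5 and 0.42 at ρ = 0.7.

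**6. Check by simulation.** In 400 simulated trials per setting (356 per arm, unstructured covariance, equal SDs, true effect 0.20), the mean estimate without the interaction was 0.094 (ρ = 0.5) and 0.109 (ρ = 0.7). With the interaction it was 0.196 and 0.204.

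**The case against.** **The response might be the change score.** The cognition text speaks of assessing change from baseline. If change were the response, the treatment term alone would be the right contrast for the two-visit outcomes. But each patient would then have one value, and a visit effect, a patient effect and an unstructured covariance would have nothing to describe. For Fitbit, a change-score model without the interaction would still pool pre-surgery and 1 year, although the text asks about both. The wording needs correction on either reading.

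**It may be a drafting slip that an analysis plan will repair.** The Fitbit, strength and fitness model sentences lack a main verb, and three sister models are right, so a slip is plausible. It does not follow that the detail was left open: the section is headed as the statistical analysis plan and lists the model terms.

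**The between-arm change is not always stated.** This stands. It is explicit only for Fitbit. For cognition it follows from the reference to within- and between-group assessment, and for strength and fitness from Hypothesis 2 and the Reporting section.

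**The Fitbit baseline is uncertain.** This also stands. The Study calendar lists Fitbit at pre-surgery and 1 year but not at baseline, while the outcome list and the analysis text both name a baseline. How far baseline dilutes this outcome depends on how that is resolved.

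**Stronger readings a reader might infer.**
- That all four models report about half the true effect. One half is exact only for two visits with equal SDs, and the protocol gives none of the quantities needed to say more.
- That pairing a patient random effect with an unstructured covariance invalidates the models. It is redundant, but it leaves the fixed-effect estimates unchanged, and any effect on convergence is conjecture.
- That "Mean difference in reduction of tumour size between treatment arms will be analysed with an ANOVA" is an error because baseline size is not a covariate. The comparison is unbiased under randomisation, and the response measure is defined relative to baseline; adjustment is a matter of precision.

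**Conclusion.** The point holds as a should-fix. The four models as written cannot deliver the between-arm difference in change, and they differ without explanation from the three models that can. The coefficient they would report is diluted by an amount set by variances and correlations that the protocol does not give, so it has no clear clinical meaning.

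The ranges in the working rest on assumed SDs, correlations and persistence of effect, and on baseline scores being part of the response. The power figures further assume a 0.2 SD effect, complete data and an uncorrected 5% level; the planned Bonferroni correction would lower power under both models.

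A reader might infer that the trial's main conclusion is at risk. It is not: the pCR analysis is a separate logistic regression, and the sample size rests on pCR alone.

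**What to change.** - Add treatment-by-visit to the fixed effects of the cognition, Fitbit, muscle strength and cardiorespiratory fitness models.
- State that the reported effect is the between-arm contrast in change from baseline at the named visit: pre-surgery for strength and fitness, pre-surgery and 1 year for Fitbit, 1 year for cognition. The quality-of-life text already has suitable wording.
- Reconcile the Study calendar with the outcome list on whether Fitbit is recorded at baseline, since the contrast needs it.

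The model correction is a change of wording, by amendment or in a separate analysis plan. It needs no new data and no change to the sample size. It should be made before the data are analysed, so that the interaction is not seen as chosen after the results.
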